### Interventions

All individuals will receive individual dietary advice according to their specific caloric needs (to maintain or to lose weight) despite treatment group, and the following recommendations will be used to calculate the total daily calories: to weight management: 25 kcal/kg/day; to weight loss: 20 kcal/kg/day [21]. The individual distribution of macronutrients (dietary carbohydrates, protein and fats), independent of the group allocated, will be determined and calculated according to Brazilian guidelines for dyslipidemia [22], metabolic syndrome [21], hypertension [23] and diabetes [24].

Group 1 (nut supplementation, NS) will receive, in addition to dietary prescription, 1 kg of pecan nuts adequately packed for 30 days of treatment (approximately 900 g, considering an intake of 30 g/day [25]) plus educational materials concerning the adequate ingestion and storage of the nuts. Patients will be counseled about not consuming olive oil during the treatment. Group 2 (olive oil supplementation, OS) will receive, in addition to dietary prescription, 1 liter of extra-virgin olive oil adequately packed for 30 days of treatment (approximately 900 ml, considering an intake of 30 ml/day [25]) plus educational materials concerning the adequate ingestion and maintenance of the olive oil. Patients will be advised to not consume mixed nuts and oilseeds during the study period. Group 3 (control diet, CD) will receive standard dietary advice according to Brazilian guidelines [21–24] and will be discouraged from using olive oil, nuts and oilseeds during this period.

### Assessment tools and variables

#### Demographic variables

A structured questionnaire will be administered to all participants for collection of demographic parameters (age, sex, ethnicity), socioeconomic and educational data.

#### Genetic data

Deoxyribonucleic acid (DNA) will be isolated from a 5-ml venous blood sample by means of a specific toolkit according to the manufacturer’s instructions. The detection of polymorphisms and genotype characterization will be performed from frozen blood samples at −80 °C by means of the TaqMan® SNP Genotyping Assay according to the manufacturer’s instructions and to the available protocol. For each gene, a different genotyping assay kit will be used: ID C_30301828_10 to detect the G allele in rs8069645 *STAT3* and ID C_ 8314999_10 to detect the A allele in rs1761667 *CD36*.

#### Clinical and behavioral variables

Medical history: data on CAD specifications, history of present illness, past medical history, history of previous outcomes (i.e., heart attack and stroke) and current medications will be collected during the patient interview. Hypertension, type-2 diabetes mellitus and dyslipidemia will be considered present according to previous diagnosis and/or the use of medications to treat each of these conditions.

Blood pressure: systolic and diastolic blood pressure will be evaluated using an automatic validated monitoring device (OMRON® HEM-7200) with an adequately sized cuff to the arm circumference, according to the guidelines [23].

Body weight and height: weight (kg) will be measured with participants barefoot, wearing minimal clothing, and standing at the center of a digital platform scale; height (cm) will be obtained with participants barefoot in the standing position, and with both arms hanging freely at the side with palms facing thighs.

Waist, hip and neck circumferences: waist circumference (cm) will be obtained with a plastic, flexible measuring tape at the middle point between the lower costal margin and the iliac crest in a perpendicular plane, with the patient standing on both feet, approximately 20 cm apart, and with both arms hanging freely. Hip circumference will be measured at the level of the widest circumference over the buttocks with the research assistant kneeling at the side of the participant, so that the level of maximum extension can be seen. Neck circumference (cm) will be measured with the head straight and eyes staring forward, horizontally, 1 inch above the laryngeal prominence.

Smoking and alcohol intake: smoking will be defined as a categorical variable (never, current or past smoking) and excessive alcohol intake will be detected if participants have a consumption of 30 g or more and 15 g or more of ethanol a day for men and women, respectively [26].

Dietary evaluation: food intake will be evaluated by means of 24-h dietary recalls (24-HDRs). Caloric intake and nutrients will be estimated by Avanutri Revolution® Nutritional Evaluation software (Rio de Janeiro, Brazil) [27].

Physical activity: levels of physical activity will be evaluated according to the International Physical Activity Questionnaire (IPAQ) short version [28] translated and validated into the Portuguese language.

#### Laboratory variables

Blood samples will be collected by a trained professional at baseline and after 12 weeks. Samples will be centrifuged at 22 °C, 2000 rpm, for 10 min and stored in Eppendorf tubes at −80 °C for later analysis.

Lipid profile: total cholesterol, low-density lipoprotein cholesterol (LDL-c) and serum triglycerides will be evaluated by the enzymatic colorimetric method; high-density lipoprotein cholesterol (HDL-c) will be evaluated by the immunoprecipitation method (Roche Modular P Chemistry Analyzer®).

Inflammatory profile: interleukin-6 (IL-6), interleukin-10 (IL-10) and tumor necrosis factor alpha (TNF-α) will be evaluated by enzyme-linked immunosorbent assay (ELISA) using commercial kits (R&D Systems, Inc., Minneapolis, MN, USA), and according to the manufacturer’s instructions in a spectrophotometer (SpectraMax M2®). High-sensitivity C-reactive protein (hs-CRP) will be evaluated by the turbidimetric technique (Roche Cobas Integra 400 Plus Chemistry Analyzer®). Fibrinogen will be evaluated by the coagulometric method (Sysmex CA-600 systems®).

Glycemic profile: fasting glucose will be evaluated by the enzymatic colorimetric method (Roche Modular P Chemistry Analyzer®). Glycated hemoglobin will be evaluated by the immunoturbidimetric method (Roche Cobas Integra 400 Plus Chemistry Analyzer®). Serum insulin will be evaluated by electrochemiluminescence technique (Roche Elecsys 2010 Immunoassay Analyzer®).

### Outcome measures

#### Primary outcome

The primary outcome measure will consist of changes in LDL-c (mg/dl) from baseline to 12 weeks.

#### Secondary outcomes

Changes in other lipid measures (total cholesterol, HDL-c, serum triglycerides) and inflammatory profiles (hs-CRP, IL-6, IL-10 and TNF-α) from baseline to 12 weeks.Changes in glycemic profile (fasting glucose, serum insulin and glycated hemoglobin), anthropometric indexes (weight, BMI and waist and neck circumferences) and in systolic and diastolic blood pressure from baseline to 12 weeks.

Patients will be prompted to complete the follow-up; if this is not possible, a 12-week visit will be scheduled for blood collection and measurements of primary and secondary outcome variables.

### Sample size

Sample size calculation was carried out in the WinPepi 11.20 for Windows program (Brixton Health, Israel). We used the data reported by Casas et al. [9], which assessed the effectiveness of a Mediterranean Diet pattern compared to a control diet among 164 individuals at high risk for cardiovascular disease. For a significance level of *α* = 0.05 and a statistical power of 80 %, with a between-group difference corresponding to a reduction of 13 mg/dl in the primary outcome (LDL-c) and considering no differences between olive oil and nut diets, the minimum sample size would be 171 patients (57 randomized to each group). Considering an expected loss rate of 20 % of patients, the total sample size needed will be 204 patients.

The allele frequency of the rs1761667 G>A and rs8069645 A>G SNPs in a Brazilian population is unknown. Since, in other studies, a frequency of approximately 40 % for each allele (A and G) has been found [23, 24], we expect that 204 individuals will provide a statistical power of 95 % in this analysis.

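### With the stated 20 % loss, 204 patients leave about 163 evaluable, short of the stated minimum of 171; power is then about 78 %, not 80 % (minor correction)

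*Protocol article*

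**What the plan says.** All the figures stand in the Sample size section of the protocol article.

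- Error rate and power: "For a significance level of *α* = 0.05 and a statistical power of 80" %. Whether the test is one- or two-sided is not stated.
- Effect: "a between-group difference corresponding to a reduction of 13 mg/dl in the primary outcome (LDL-c"), with the two supplemented diets treated as equivalent ("considering no differences between olive oil and nut diets").
- Size before losses: "the minimum sample size would be 171 patients (57 randomized to each group").
- Loss: "Considering an expected loss rate of 20 % of patients".
- Size after losses: "the total sample size needed will be 204 patients".

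No standard deviation is given, and no other section states a different loss rate or total. The same section uses 204 again for its statement of 95 % power in the genetic analysis.

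**The concern.** A loss rate is a share of the patients who enter the trial. To have 171 left after losing 20 %, the starting number must be 171 divided by 0.80. The stated 204 is lower than that, so the minimum of 171, the loss of 20 % and the total of 204 cannot all be right.

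At stake is whether the recruitment target delivers the stated power for the primary outcome at the loss rate the authors themselves expect. The target also decides when recruitment stops, and the Discussion describes the trial as adequately powered.

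**Working it through.** **Inputs (Sample size section).** Minimum 171, or 57 per group; loss 20 %; total 204; difference 13 mg/dl; alpha 0.05; power 80 %. Assumed, because not stated: a two-sided test, and a standard deviation back-solved from the plan's own figures.

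**1. Reproducing 204.**
- Multiplying per group: 57 × 1.20 = 68.4, cut to 68; 68 × 3 = 204. This matches exactly.
- Multiplying the total: 171 × 1.20 = 205.2. This is close but does not match.
- Dividing the total: 171/0.80 = 213.75, so 214. This does not match.
- Dividing per group: 57/0.80 = 71.25, so 72; 72 × 3 = 216. This does not match.

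Per-group multiplication with rounding down is therefore the likely route. It is an inference from the match, since the article shows no step.

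**2. What 204 leaves.**
- 204 × 0.80 = 163.2 patients; 163.2/3 = 54.4 per group.
- Shortfall against the minimum: 171 − 163.2 = 7.8 evaluable patients.
- Largest loss that still leaves 171: 1 − 171/204 = 16.2 %.

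**3. What would leave 171.**
- 214 × 0.80 = 171.2.
- In equal arms, 72 × 0.80 = 57.6 per group, 216 in total.
- The gap from 204 is 10 randomised patients, or 12 in equal arms.

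**4. Effect on power.** Take 57 per group as giving exactly 80 % power for one pairwise comparison.
- Implied SD (normal formula): 13 / [(1.96 + 0.8416) × √(2/57)] = 24.77 mg/dl. Solving with the t distribution gives 24.56 mg/dl.
- Power at 54.4 per group (normal): Φ(2.8016 × √(54.4/57) − 1.96) = Φ(0.777) = 78.1 %.
- With the t-based SD and a t-test: 78.1 %.
- With both supplemented groups pooled against control (2:1, SD back-solved the same way): 78.1 %.
- With a three-group F test (SD back-solved the same way): 78.0 %.

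The result hardly depends on which comparison the authors had in mind. The loss is about 2 percentage points.

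**The case against.** The strongest case on the other side is about weight and consequence, because the arithmetic in the article cannot be rescued.

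- **Actual losses may be lower than 20 %.** The Secondary outcomes section schedules a 12-week visit for blood collection and outcome measurement in patients who cannot complete follow-up. Some who stop the diet may still supply the primary outcome. This stands as a practical point, but the sample size text still assumes 20 %.
- **The planned analysis may be more precise than the calculation.** The Statistical analyses section plans ANCOVA on the change, with adjustment that may include baseline values. If the back-solved SD is unadjusted, a covariate correlation of 0.2 would give 79.8 % at 54.4 per group, and 0.3 would give 81.8 %. The article states no correlation, so this is an assumption. It does not repair the stated figure.
- **The authors may have meant a 20 % margin on top of 171.** The text describes a loss rate among patients, not a margin. A 20 % margin on 171 would also be 205.2, slightly above 204.
- **The mechanism is not documented.** A reader might infer that the authors demonstrably multiplied where they should have divided. The article does not show this; it is only the likeliest explanation. The inconsistency holds whatever the cause.
- **The power loss can be overstated.** A reader might arrive at about 77 %. That figure (77.4 %) comes from putting the SD derived with the normal formula into a t-test, a pairing that gives only 79.3 % at the plan's own 57 per group. With SD and test matched, the answer is about 78 %.

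**Conclusion.** The stated total is wrong on the section's own inputs: 204 patients less 20 % leaves about 163, not 171. This part needs no outside assumption. The size is minor: 10 randomised patients too few (12 in equal arms), and power of about 78 % instead of 80 %. The total of 204 is sufficient for losses up to about 16 %.

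The power figure rests on taking 57 per group as exactly 80 % power, on a two-sided 5 % test, and on a back-solved SD of about 24.6 to 24.8 mg/dl for the pairwise comparison. The 171 itself cannot be checked, because no SD is given.

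A reader might infer that the trial is materially underpowered or that its design is compromised. The documents do not support that. A drop of about 2 points changes no analysis, allocation or outcome.

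**What to change.** Make one of two changes in the Sample size section.

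1. Keep 204, and state that it gives about 78 % power at 20 % loss and 80 % only for losses up to about 16 %.
2. Correct the stated total to 214, or 216 if the arms are to be equal.

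The first costs one sentence and a slightly less favourable power statement, and recruitment does not change. The second adds 10 to 12 patients. It is still open, because the Trial status section reports 120 patients completed and recruitment continuing. If the total changes, the genetic power sentence that reuses 204 should be updated with it.

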### Study objectives

The primary objective of this randomized-controlled clinical trial is to evaluate the effect of three dietary approaches on metabolic, inflammatory and anthropometric profiles in patients with CAD after 12 weeks. The secondary objective is to detect an interaction of patients’ response to these three dietary approaches with polymorphisms in the *CD36* and *STAT3* genes.

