### Statistical analyses

All data will be double-checked prior to statistical analyses. Baseline demographic and clinical characteristics of the participants according to groups will be analyzed using descriptive statistics, and inferential statistics will be employed to compare the effects of the dietary interventions on the different outcome measures. Continuous variables following a normal distribution will be expressed as mean ± standard deviation and asymmetrically distributed continuous variables will be expressed as median and interquartile range. Categorical variables will be expressed as absolute and relative frequencies. Departure of genotype distributions from the Hardy-Weinberg equilibrium in all participants will be assessed using chi-square tests. For between-group comparisons, analysis of variance (ANOVA) and the Kruskal-Wallis H test will be used for variables with normal and asymmetric distribution, respectively. The chi-square or Fisher’s exact tests will be used to evaluate categorical variables. All relevant endpoints (new cardiovascular events and death) will be registered as absolute number and percentages according to groups. The generalized estimating equations (GEE) model under the missing-at-random assumption will be used for comparison between outcome variables during the study period. Delta from all outcome data will be obtained from the difference between the measure at 12 weeks and baseline, and will be compared according to groups using analysis of covariance (ANCOVA), adjusted for potential confounders (for instance, differences in baseline data). The SNPs will be included in all ANCOVA models as interaction variables. There is no interim analysis planned. The significance level will be set at 5 %, and all data will be analyzed in SPSS 18.0 (SPSS Inc., Chicago, IL, USA) according to intention-to-treat.

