The randomized controlled GENUTRI trial is designed to explore three different dietary approaches for cardiometabolic and inflammatory profile improvement in patients with established CAD. The dietary approaches suggested by the Brazilian guidelines for individuals at very high cardiovascular risk are largely recommended in our country, and consist of 50–60 % of dairy energy from carbohydrates, 10–15 % from proteins, 25–35 % from total fats, <7 % from saturated fatty acids (SFA), <20 % from MUFA, <10 % from PUFA, <1 % from trans fats, <200 mg/day from dietary cholesterol, 20–30 g/day from fiber and <2400 mg/day of sodium [21–24]. In Brazil, the effects of a modified MeDiet were evaluated by only one small study with 40 CAD patients, with mixed and inconsistent results [36]. The GENUTRI study is the first adequately powered clinical trial focusing on nuts or olive oil supplementation in a southern Brazilian population. Since it may be difficult for Brazilian individuals to adhere to and maintain a traditional MeDiet pattern, the study findings will have important implications not only for our population but also for the feasibility of other potential applications for the long-term prescription of cardioprotective foods in individuals with CAD. Additionally, we will try to demonstrate that genetic polymorphisms linked to cardiovascular disease may modulate the effects of different diets on biochemical and inflammatory markers.

A large randomized clinical trial has been recently proposed in patients with CAD based on novel dietary interventions with the potential for low cost and high feasibility for use in Brazil [37]. However, this protocol does not consider genetic differences regarding the interbred Brazilian population. The GENUTRI trial aims also to stimulate the consumption of local foods since the olive oil and pecan nuts provided in the study are cultivated and produced in our country by farmers on a small scale. If effective, it may contribute to economic growth in southern Brazil by encouraging the consumption of these foods. Besides, our results may generate hypotheses for larger randomized clinical trials regarding nutrigenetic approaches in different Brazilian regions.

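### The 95% power stated for the SNP analysis comes with no effect size, SD or genetic model, and the plan's own figures do not support it for the planned diet-by-genotype interaction

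*Protocol article*

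**What the plan says.** The Sample size section of the protocol article has two parts. The first sizes the diet comparison. Its target is "a statistical power of 80" per cent, and the assumed effect is an LDL-c difference between groups of 13 mg/dl. The two active diets are treated as equivalent: "considering no differences between olive oil and nut diets". This gives 57 patients per group, 171 in all, raised to 204 for an expected 20% loss. The second part turns to the two SNPs. It notes that their frequency in Brazil is unknown, takes about 40% from other studies, cited as [23, 24], and concludes: "we expect that 204 individuals will provide a statistical power of 95 % in this analysis". It does not say which analysis is meant.

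Study objectives supplies the target: "The secondary objective is to detect an interaction of" diet response with the *CD36* and *STAT3* polymorphisms. Statistical analyses enters the SNPs into the ANCOVA models as interactions. The only other SNP analysis named is the Hardy-Weinberg check. Interventions uses [23] and [24] for the hypertension and diabetes guidelines.

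**The concern.** Power cannot follow from an allele frequency and a sample size alone. It also needs an effect size, a residual SD, a genotype coding and a contrast, and none of these is stated for the SNP analysis. The figure also counts all 204 patients, although the preceding paragraph expects to lose a fifth of them.

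The size of the claim is surprising too. The same 204 patients give about 86% power for a plain 13 mg/dl difference between two diets if nobody is lost. An interaction of equal size splits each arm by genotype, so it must have much less power than that.

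The gene-diet interaction is a secondary objective, but the Abstract and Background present it as the purpose of the study. If a power of 95% stays on record, a non-significant interaction could be given more weight than the data can bear.

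**Working it through.** **Inputs from the protocol article.** 57 per arm, 13 mg/dl and 80% power; 204 randomised; 20% loss; allele frequency about 40% (all Sample size). "The significance level will be set at 5" per cent (Statistical analyses).

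**Assumptions, because the article is silent.** Two-sided test; equal arms (68 each); Hardy-Weinberg proportions; interaction size set to 13 mg/dl; SD back-solved as below.

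**Genotype shares.** Carriers 1 − 0.6² = 64%, non-carriers 36%, variant homozygotes 0.4² = 16%.

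**SD.** Solving the two-sample t-test for 57 per arm, 13 mg/dl and 80% power gives SD = 24.56 mg/dl. The normal approximation, 13 × √(57/2) / (1.960 + 0.842), gives 24.8.

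**Reproducing the 95%.** Take a SNP main effect, carriers against non-carriers, pooled over diets, with no loss:

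- Group sizes are 204 × 0.64 = 130.6 and 204 × 0.36 = 73.4.
- SE = 24.56 × √(1/130.6 + 1/73.4) = 3.58.
- Power = Φ(13/3.58 − 1.96) = 95.2% (95.1% by the t-test).
- With 204 × 0.8 = 163 evaluable, SE = 4.00 and power is 90%.
- With recessive coding and all 204, it is 79%.

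**The planned interaction.** With p the share in one genotype group and n₁, n₂ the patients in the diets compared:

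SE = SD × √[(1/n₁ + 1/n₂) × (1/p + 1/(1−p))]; power = Φ(13/SE − 1.96); interaction detectable with 95% power = (1.960 + 1.645) × SE.

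For example, with carrier coding and one active arm against control at 68 each, SE = 24.56 × √[(2/68) × (1/0.64 + 1/0.36)] = 8.77, and power = Φ(1.48 − 1.96) = 31.6%.

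| Coding | Contrast | N | SE | Power at 13 mg/dl | Detectable at 95% power (mg/dl) |
|---|---|---|---|---|---|
| Carrier | one active arm vs control | 204 | 8.77 | 31.6% | 31.6 |
| Carrier | active arms pooled vs control | 204 | 7.60 | 40.2% | 27.4 |
| Carrier | one active arm vs control | 163 | 9.81 | 26.3% | 35.4 |
| Carrier | active arms pooled vs control | 163 | 8.50 | 33.4% | 30.6 |
| Recessive | one active arm vs control | 204 | 11.49 | 20.4% | 41.4 |
| Recessive | active arms pooled vs control | 204 | 9.95 | 25.7% | 35.9 |
| Recessive | one active arm vs control | 163 | 12.84 | 17.2% | 46.3 |
| Recessive | active arms pooled vs control | 163 | 11.12 | 21.4% | 40.1 |

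**Sensitivity, all at N = 204.**

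- Other readings of the primary calculation give SDs from 21.4 (Bonferroni for three comparisons) to 28.6 (2:1 pooled contrast). Over both codings, power is then 16–50%.
- The most favourable two-group case (SD 21.4, pooled diets, 50/50 genotype split) gives 53%.
- The omnibus interaction test at SD 24.8 gives 19–31% with two genotype groups and 15–25% with three.
- Additive coding at 6.5 mg/dl per allele gives 18–23%. At 13 mg/dl per allele it gives 56–69%, but that means 26 mg/dl between homozygotes, twice the diet effect.
- For 95% power at 13 mg/dl with carrier coding, the SD would have to be about 10–12 mg/dl, less than half the implied value.

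**The case against.** The sentence names no test, and a SNP main effect with the implied SD, 13 mg/dl and all 204 patients lands on 95%. The figure may therefore have been calculated correctly for a different question. That stands as a likely explanation, though the text cannot confirm it. It does not rescue the claim: no main-effect hypothesis is among the objectives, and even that figure ignores the expected loss.

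The 13 mg/dl is the assumed difference between diets. The article states no interaction size, so a reader who says that the trial has 20–40% power at its own interaction effect goes too far. The percentages are conditional on my choice of effect, on a back-solved SD and on the coding. Covariate adjustment would also help: if covariates explained 40% of the variance (an assumption) and the implied SD is unadjusted, carrier-coded power with all 204 would be 48–60%. This widens the range but does not bring it to 95%.

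A reader might also set this against the Discussion's statement, "The GENUTRI study is the first adequately powered clinical trial". That sentence goes on to speak of nut or olive oil supplementation, so it concerns the diet comparison, and nothing here contradicts it. The Discussion also says that the results may generate hypotheses for larger nutrigenetic trials, which tempers the risk of over-reading a null result.

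Finally, one might infer that the allele-frequency citation is wrong. The reference list is not shown, so the clash with Interventions supports only a check of the citation. It has no bearing on power.

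**Conclusion.** The point holds in this form: 95% power is stated without the inputs that define it, and it cannot be attached to the diet-by-genotype interaction, the only outcome analysis planned for the SNPs. If the interaction equals the 13 mg/dl diet effect and the SD is about 24.6 mg/dl, power is roughly 20–40% with all 204 patients and 17–33% with 163. No interaction variant that was run exceeded 69%, and that one needed twice the effect between homozygotes. No adjustment was made for testing two SNPs; one would lower power further.

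The exact percentages rest on the listed assumptions; the direction does not. The statement should be corrected, but it concerns a secondary objective. The sample size, the primary outcome and the primary analysis are unaffected.

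**What to change.** In Sample size:

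- Delete the 95%, or attach it explicitly to a carrier against non-carrier main effect with its effect size, SD, coding and N, and add the figure after loss (about 90%).
- For the interaction, state power or the detectable difference together with the SD and its source, the genotype coding, the contrast and the evaluable N. For example: with an SD of 24.6 mg/dl back-calculated from the primary sample size, a 40% allele frequency, carrier coding and a two-sided 5% test, 95% power requires a difference in diet effect of about 27–32 mg/dl with 204 evaluable patients and 31–35 mg/dl with 163 (lower figure active arms pooled, upper figure one active arm against control). Recessive coding needs about 36–41 and 40–46 mg/dl.
- Check the [23, 24] citation for the allele frequency.

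In Statistical analyses, label the SNP interaction analyses exploratory and report them as estimates with 95% confidence intervals.

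The cost is about a paragraph of wording and a less favourable stated power. No patients or procedures are added. Recruitment is still under way, so the change can be made before the analysis.
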